### Outcomes

The main primary outcome of the study will be symptom severity, which will be measured by the VISA-A questionnaire. Pain will be assessed by the VAS where 0 represents no pain and 10 represents the worst pain imaginable [29]. Pain will be assessed during the heel rise test and during the single-leg drop vertical jump test [30,31] (described below). Participants will also be asked about their worst pain in the previous week [23]. Symptom severity will be evaluated with the Brazilian Portuguese version of the VISA-A questionnaire [32]. Improvements greater than 3 points in the VAS [33] and greater than 14 points in the VISA-A are considered clinically meaningful [24,33]. Symptom severity and pain will be assessed before the interventions (baseline), at week 6, at week 12 (end of the interventions), and 6 months after the end of the interventions (follow-up).

Secondary outcomes will include peak isometric strength of hip and knee extensors and ankle plantar flexors, function of the plantar flexor muscles (heel rise test and single-leg drop vertical jump test), quality of life, and perception of improvement or worsening of the participants’ condition.

A handheld dynamometer (Lafayette Instruments, IN, USA) will be used to measure the peak isometric strength of the hip extensors, knee extensors, and ankle plantar flexors [34]. Inelastic straps will be used to stabilize the participants and to fixate the dynamometer, to eliminate the effect of the evaluator’s strength in the tests [34,35]. A detailed description of the assessments is presented in the Supplementary Material (S3 File). For each test, one practice and 3 valid trials will be performed. Each trial will consist of 5s maximal contraction, with 15s of rest between trials. The peak-force values produced during each of the 3 trials will be recorded. Peak-force values (kg) will be converted to Newtons (kg x 9.81) to achieve a unit of force. Newtons will then be converted to torque values [force (N) x action length of the segment (m)]. The action length of the thigh, shank, and foot will be measured as previously described (S3 File) [35], for the calculation of the hip extensor torque, knee extensor torque, and ankle plantar flexor torque, respectively. Finally, the torque data will be normalized against each participant’s body mass. The average normalized peak torque values obtained during the 3 trials will be used for analysis [34,35].

To evaluate the function of the plantar flexor muscles, two tests will be carried out: the heel rise test and the single-leg drop vertical jump test [31,36]. A detailed description of the tests is presented in the S3 File. The Calf Raise application will be used to measure the maximal number of repetitions and the total work (Joules) during the heel rise test [37], which will be used for analysis. Three repetitions of the single-leg drop vertical jump test will be performed, and the average height will be used for analysis (S3 File). Immediately after the performance of the heel rise test and the single-leg drop vertical jump test, participants will be asked to rate the Achilles tendon pain that they felt during the test in the 0–10 VAS [36].

The Global Rating of Change (GROC) will be used to assess the participant’s perception of improvement or worsening after the interventions [38]. Changes of 4 points or more have previously been considered clinically important in patients with Achilles tendon pain [38,39]. Finally, to assess the impact of Achilles tendinopathy on participants’ quality of life, the Short-Form Health Survey (SF-12) will be used [40,41]. Secondary outcomes will be assessed before the interventions (baseline) and immediately after 12 weeks of interventions, except for the GROC, which will be evaluated only at the 12-week timepoint. The SPIRIT flowchart (Fig 1) illustrates the sequence of activities that will be performed during the study.

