**Methods:**

Sixty amateur runners will be randomly allocated to one of two groups: high-load exercise group (HLG) and moderate-load exercise group (MLG). The HLG will start the treatment with calf exercises with 55% of 1 repetition maximum (1RM) and progressively increase the exercise load in 12 weeks to 90% 1RM. The MLG will perform exercises with 55% 1RM during the 12 weeks of intervention. The RM load will be reassessed every 2 weeks, and the total training volume (total repetitions and tendon time under tension per week) will be the same in both groups. Both groups will also perform strengthening exercises for the quadriceps and gluteal muscles. The primary outcome will be symptom severity (Victorian Institute of Sport Assessment−Achilles), which will be evaluated at baseline, at week 6, at week 12 (end of intervention), and 6 months after the intervention. Pain will be evaluated using the visual analogue scale during the same time points. Secondary outcomes will include peak isometric strength of ankle, knee, and hip muscles, function of plantar flexor muscles, quality of life, and perception of improvement. Results will be analyzed under the intention-to-treat principle using generalized estimating equations (GEE) and Bonferroni-adjusted post hoc tests.

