A few studies have evaluated the variation in progressive loading parameters [13,14], such as the number of repetitions, sets, frequency, and load, to find an ideal exercise dose and load magnitude during interventions in patients with tendinopathy [15]. Recently, Arampatzis et al. [16] suggested that when comparing exercise programs with the same volume, but with different loads, only protocols with greater load produce adaptations in the tendons, such as increased stiffness and increased cross-sectional area in people with healthy Achilles tendons. It is believed that this occurs because high-magnitude contractions cause deformation (strain) of the tendon within the range considered ideal (between 4.5 and 6%) for positive mechanical and morphological adaptations [16]. High-load exercises (90% of 1 repetition maximum (1RM)), in addition to improving strength and generating hypertrophy, can cause an effective mechanical stimulus in the Achilles tendon that stimulates beneficial adaptations in the tissue, causing improvement in the mechanical properties of healthy Achilles tendons [16,17]. The same research group has observed, in a non-randomized controlled study, that an intervention involving isometric exercises performed at 90% 1RM resulted in more structural adaptations in the Achilles tendon of patients with Achilles tendinopathy when compared with the Alfredson protocol and with passive treatments [18]. However, recent evidence suggests that tendon structural adaptations also occur in tendinopathic patellar tendons in response to moderate-load progressive exercises (55% 1RM) [13,19,20].

To our knowledge, however, the effects of exercises with different load magnitudes on individuals with Achilles tendinopathy remain unknown. The primary objectives of the study will be to verify the short-term (6 and 12 weeks) and long-term (6 months) effects of moderate-load calf exercises compared to high-load calf exercises in amateur runners with Achilles tendinopathy in terms of pain and severity of symptoms. The secondary objectives will be to verify the effect of the interventions on strength, muscle function, and quality of life in runners with Achilles tendinopathy.

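### VISA-A clearly leads, but the rank of pain and the primary time point are stated inconsistently, so a pain result could be claimed as meeting a primary objective when VISA-A is null

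*Protocol article*

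**What the plan says.** The protocol article describes the primary question in four places.

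- **Abstract, Methods.** One outcome: "The primary outcome will be symptom severity" (VISA-A), measured at baseline, week 6, week 12 and 6 months after the intervention. Pain comes next, ahead of the secondary outcomes and without a rank: "Pain will be evaluated using the visual analogue scale during the same time points".
- **Introduction, last paragraph.** Several objectives: "The primary objectives of the study will be to verify the short-term (6 and 12 weeks) and long-term (6 months) effects" of the two loads "in amateur runners with Achilles tendinopathy in terms of pain and severity of symptoms". The secondary objectives are strength, muscle function and quality of life.
- **Outcomes.** "The main primary outcome of the study will be symptom severity, which will be measured by the VISA-A questionnaire". The same paragraph brings in three VAS ratings: "Pain will be assessed during the heel rise test and during the single-leg drop vertical jump test", and "Participants will also be asked about their worst pain in the previous week". Pain has its own threshold for a meaningful change (3 points) and the same four assessments as VISA-A. The secondary list that follows does not contain pain, and the section later schedules the secondary outcomes at baseline and week 12 only (GROC at week 12 only).
- **Sample size calculation.** A 14-point VISA-A difference at 12 weeks, giving 54 evaluable and 60 recruited.

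The Statistical analysis section applies GEE to the outcome measures, with Bonferroni-adjusted post hoc tests where appropriate. It does not rank outcomes or visits.

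**The concern.** The Introduction treats pain as primary. The Outcomes section hints that it is, because calling VISA-A the *main* primary outcome suggests there are others, and because pain is neither listed nor scheduled with the secondary outcomes. The abstract does not treat it as primary. For the time point, the Introduction puts three visits on an equal footing, while the sample size rests on one.

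This matters when the results are read. Suppose VISA-A shows no difference at week 12 but one pain rating does at some visit. On the Introduction's wording the authors could report that a primary objective was met; on the abstract's wording they could not. A reader could not tell from the published protocol which claim was planned, and the error rate behind the headline claim would depend on which wording was followed.

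**Working it through.** **1. The plan's own figure.** 54 / (1 − 0.10) = 60, as stated. The standard deviation is not given, so 54 cannot be checked directly. Taking two-sided α = 0.05 (an assumption; sidedness is not stated), 80% power and 27 per group, the normal approximation gives SD = 14 × √(27/2) / (1.960 + 0.842) = 18.4. The calculation provides for one comparison, VISA-A at week 12, at the full α.

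**2. How many comparisons could be called primary.**
- Abstract: VISA-A, 1 outcome.
- Introduction, with pain measured as in the Outcomes section: VISA-A + 3 VAS ratings = 4 outcomes. With 3 post-baseline visits, 4 × 3 = 12 between-group comparisons.
- Two of the VAS ratings are taken during the heel rise and drop jump tests. These are secondary function outcomes, and the secondary schedule has them at baseline and week 12 only. On that schedule the count is 3 + 3 + 1 + 1 = 8.

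Twelve is therefore an upper bound, not a number that the plan states.

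**3. Chance of at least one false positive if all four outcomes count.** With each outcome held at 5% and independence, 1 − 0.95^4 = 18.5%. Real outcomes are correlated, so this was also simulated: 400,000 draws of 12 normal test statistics under no effect. All correlations are assumptions, with 0.5 between visits.

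| Correlation between outcomes | Bonferroni over 3 visits within each outcome | Week 12 only, each outcome at 5% |
|---|---|---|
| 0 | 16.6% | 18.5% |
| 0.3 | 15.8% | 17.4% |
| 0.5 | 14.4% | 15.5% |
| 0.7 | 12.3% | 12.9% |

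VISA-A alone, with Bonferroni over its 3 visits, gives about 4.5%. The excess comes from the unsettled rank of pain rather than from the repeated visits.

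**4. Dependence on how the post hoc tests are used.** Suppose post hoc tests are run only after a significant group-by-time interaction (four time points, same assumed correlations, outcome correlation 0.3 to 0.7). The chance of any false post hoc finding across the four outcomes is then about 3% to 4%. If a significant interaction on any one of the four outcomes is itself taken as a positive finding, the chance is about 13% to 18%. The Statistical analysis section does not say which use is meant.

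**5. What making everything primary would cost.** Bonferroni over 12 gives α = 0.05/12 = 0.00417, with critical value 2.865. At SD 18.36, n = 2 × 18.36² × (2.865 + 0.842)² / 14² = 47.3, so 48 per group: 96 evaluable, and 96 / 0.90 = 107 recruited. With 27 per group the power falls from 80% to about 47%. The trial is sized for one primary comparison.

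**The case against.** The strongest reply is that nothing is in doubt about the primary outcome. VISA-A is the only measure called a primary outcome anywhere, and it alone sets the sample size. The Introduction states objectives, not outcomes, and the secondary list is worded as open, so leaving pain out does not promote it. This stands as far as it goes: the documents do not dispute which outcome leads. It does not settle whether a pain result can meet a primary objective, because the Introduction says that pain is part of the primary objectives and no section gives it another rank.

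A reader might infer that the trial has 12 primary comparisons and a false-positive risk of 30% or more. The documents do not support that. Twelve requires every VAS rating to be primary at every visit, which no section states. Figures of that size (about 30% to 39% at the assumed correlations of 0.3 to 0.7, visits 0.5) describe unadjusted tests, whereas Bonferroni adjustment is planned.

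A reader might also infer that the missing error control across outcomes is itself a fault. That cannot be said here. Such control is commonly left to a statistical analysis plan, and neither that nor the full ethics-approved protocol is shown. What can be said is that the article's own sections disagree.

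Finally, demoting pain is not the only consistent solution; a stated hierarchy or a split of α would also serve. True, but VISA-A at week 12 is the only choice that leaves the sample size as it is with the full α on one comparison.

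**Conclusion.** The point holds as an inconsistency over the rank of pain and the primary time point. If VISA-A and the three pain ratings are all treated as primary, the chance of at least one false positive is roughly 12% to 18% when each outcome is held at about 5%, against about 5% for VISA-A alone. This is a conditional upper range. It rests on assumed correlations, on two-sided 5% tests and on counting all three pain ratings, and it falls to about 3% to 4% if only post hoc findings that follow a significant interaction are counted. The practical risk lies in reporting: as written, the protocol lets a pain finding carry the primary claim after VISA-A has failed. It is worth correcting because the correction needs only wording.

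**What to change.** 1. Name VISA-A at week 12 as the single primary comparison, as the sample size assumes, in the abstract and the Outcomes section, and delete *main* before *primary outcome*.
2. List the three VAS pain measures and VISA-A at week 6 and at 6 months as secondary outcomes, in the abstract as well as in the Outcomes section.
3. Reword the objectives in the Introduction so that pain and the other visits come under the secondary objectives.
4. Amend the sentence in the Outcomes section that places secondary outcomes at baseline and week 12 only. Otherwise, making pain secondary creates a new contradiction with its four assessments. In the same edit, state at which visits the pain ratings during the heel rise and drop jump tests are taken.
5. State that the trial's conclusion rests on VISA-A at week 12 and that pain is supportive.

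The cost is wording, and pain loses primary status. The sample size of 54 evaluable and 60 recruited stays, and no assessment need change. The article places the last data collection in July 2026; the change should be dated and made before anyone sees results by group.

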**Fig 1 pone.0342934.g001:**
[figure not shown]
Flowchart of SPIRIT.

### Interventions

Participants of both groups will be submitted to 12 weeks of exercise-based progressive loading interventions in phases, following the recommendations of recent studies [7,42,43]. Specifically, the exercise protocol of both groups will be divided into three phases: 1) Slow-velocity progressive load exercises (3 seconds for the concentric phase and 3 seconds for the eccentric phase) with double-leg support (weeks 1–4), 2) Slow-velocity progressive load exercises in single-leg support (weeks 5–8), and 3) Plyometric exercises and running-specific strengthening exercises (weeks 9–12). The interventions of both groups are described in detail in the Supplementary Material (S4 File) following the recommendations of the Template for Intervention Description and Replication (TIDieR) [44].

Participants will be divided into two groups that will have equivalent total exercise volumes for the triceps surae: HLG which will begin triceps surae exercises with 55% 1RM in the first and second weeks, progressing to 65% 1RM in the third and fourth weeks, 75% 1RM in the fifth and sixth weeks, 85% 1RM in the seventh and eighth weeks and, 90% 1RM from the ninth week until the end of the 12 weeks of treatment; MLG which will perform triceps surae exercises with 55% 1RM during all 12 weeks of intervention (Table 1).

**Table 1 pone.0342934.t001:** Triceps surae exercise protocols for both groups.

	Weeks 1–2	Weeks 3–4	Week 5	Week 6	Week 7	Week 8	Weeks 9–12	Total Reps
HLG % 1RM	55	65	75	75	85	85	90	1,054
HLG Reps	15	15	10	8	8	6	4	
HLG Sets	3	3	3	4	4	4	5	
MLG % 1RM	55	55	55	55	55	55	55	1,053
MLG Reps	17	15	12	10	8	7	6	
MLG Sets	3	3	3	3	3	3	3	

HLG, high-load group; MLG, moderate-load group; RM, repetition maximum; Reps, repetitions.

In addition to specific exercises for the triceps surae, both groups will receive strengthening exercises for the muscles of the kinetic chain (i.e., quadriceps and gluteus maximus), which are synergists of the triceps surae during running and have been shown to have strength deficits in individuals with Achilles tendinopathy [45,46]. These exercises will be performed following the recommendations for strength training in resistance-trained individuals from the American College of Sports Medicine (ACSM) [47]. Specifically, these exercises will be performed in the following manner: in the first phase (1^st^ − 4^th^ weeks), participants will perform the exercises in 3 sets of 12 repetitions with 60% 1RM, in the second phase (5^th^ − 8^th^ weeks) they will perform the exercises in 3 sets of 10 repetitions with 70% 1RM, and in the third phase (9^th^ − 12^th^ weeks) they will perform the exercises in 3 sets of 8 repetitions with 80% 1RM [47] (S4 File).

Every two weeks, during the supervised session, a 10RM test will be performed to estimate 1RM and adjust training loads of all exercises accordingly [48,49]. In exercises where resistance will be provided by an elastic band, two levels of elastic resistance lower than 1RM will be established as the initial load, and the load will progress by increasing 1 level of elastic resistance [50].

Participants of both groups will be instructed to refrain from performing intense physical activities that may overload the Achilles tendons (i.e., daily running) during the duration of the study. If they are unwilling to do so, they will be asked to refrain from such activities for the first 3 weeks of treatment [23]. After this period, they will be allowed to resume their running routine using the pain monitoring model as a guide, i.e., avoid running distances/intensities that cause their pain to increase to more than 4/10 during or in the day after the run [51].

Interventions will take place 3 days a week on alternating days for twelve weeks. At least one of the weekly treatment sessions will be carried out with supervision [13]. Supervision will be carried out in person by experienced physical therapists trained in the clinical trial protocols. For the other two weekly non-supervised sessions, participants will receive illustrated material with guidance on the exercise parameters they should perform (S4 File). Adherence to exercises during non-supervised sessions will be monitored through a training diary, where participants will record the exercises performed and the training load.

In Phase 3 (9^th^ − 12^th^ weeks), participants will perform plyometric exercises during the supervised training session, given that individuals with Achilles tendinopathy have been shown to exhibit deficits in muscular power [52]. Plyometric training is considered one of the most effective modalities to counteract this impairment [53]. In the remaining two weekly sessions, participants will continue with the Phase 2 exercise protocol, with progressive adjustments to load, sets, and repetitions, as outlined in Table 1.

### Monitoring for adverse events

All participants will use a training diary to record the non-supervised sessions. Training records will include information on training intensity (repetitions, sets, and loads), sessions, soreness during training (VAS), and deviations from planned intervention protocols [13].

If any adverse events occur during or after the intervention, the participant will be advised to contact one of the physical therapists responsible for the intervention. The adverse events will be registered in detail and described at the conclusion of the study. Participants will be instructed not to perform any other type of treatment and not to use analgesic medications during the study period. If any pain medication or analgesic modality is used during the intervention period, the participants will be instructed to take note of the quantity and dosage of each medication and the parameters of the analgesic resource, reporting this information in the post-intervention assessments [54].

### Statistical analysis

The data will be analyzed by a researcher who will remain blind to group allocation. The Statistical Package for the Social Science software (version 17.0; SPSS Inc, Chicago, IL) will be used to analyze the results. To assess the normality of data, the Shapiro-Wilk test will be used. Outcome measures will be analyzed using generalized estimating equations (GEE) to identify main effects of group and time, and group-by-time interactions. Bonferroni-adjusted post hoc tests will be used when appropriate. The results will be presented as mean differences and 95% confidence intervals (CI). All data will be analyzed using the intention-to-treat principle, and in the event of missing data, a regression-based imputation technique will be used [55].

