### Sample size calculation

To determine the study sample size, a calculation was made considering a confidence level (α) of 95%, a power (β) of 80%, and a difference between groups in the Victorian Institute of Sport Assessment-Achilles (VISA-A) at 12 weeks of 14 points [24]. The standard deviation used in the calculations was obtained from a similar clinical trial that used this same variable as the primary outcome [23]. Using this information, calculations for linear mixed models indicated a sample size of 54 individuals (27 per group). Considering a loss of 10%, we reached a total number of 60 individuals, with 30 in each group.

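### As written, the GEE model treats baseline as a time level and does not adjust for it; adjusting for baseline VISA-A would sharpen the week-12 comparison at almost no cost

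*Protocol article*

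**What the plan says.** The Statistical analysis section of the protocol article gives one model for all outcomes: "Outcome measures will be analyzed using generalized estimating equations (GEE) to identify main effects of group and time, and group-by-time interactions". Where appropriate, post hoc tests with a Bonferroni correction are to follow. The article mentions neither a covariate nor a constraint on the baseline means.

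The Outcomes section names the main outcome ("The main primary outcome of the study will be symptom severity, which will be measured by the VISA-A questionnaire") and gives its schedule: "Symptom severity and pain will be assessed before the interventions (baseline), at week 6, at week 12 (end of the interventions), and 6 months after". That last visit is timed from completion of treatment. For most other outcomes there are only two occasions: "Secondary outcomes will be assessed before the interventions (baseline) and immediately after 12 weeks of interventions". GROC is the exception and is taken at week 12 only.

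The Sample size calculation section targets a 14-point between-group VISA-A difference at 12 weeks. It arrives at 27 per group, raised to 30 per group for 10% loss, and mentions no baseline adjustment.

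**The concern.** The article never says in one sentence that baseline is a level of the time factor, but its sections together all but force that reading. Strength, function and SF-12 have one follow-up visit. A time effect or a group-by-time interaction can exist for them only if baseline is one of the time levels, and the same model is stated for every outcome.

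Under that reading the model offers two group contrasts at week 12. The post hoc between-group test is the raw difference in means and ignores baseline. The interaction contrast compares changes from baseline and subtracts baseline in full, whatever its correlation with the outcome. Neither uses baseline with the weight that minimises the variance.

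At stake is precision in a trial of 30 per group. Randomization is in blocks of four with no stratification described, so nothing in the stated design balances baseline VISA-A. A chance baseline difference moves the two contrasts in opposite directions, and the section does not say which of them answers the primary question.

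**Working it through.** **Inputs from the article.** Target difference 14 points at 12 weeks; 27 per group evaluable, 30 per group enrolled; 80% power; 95% confidence, taken here as two-sided alpha 0.05 (sidedness is not stated).

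**Inputs not in the article, so assumed.** The SD; the correlation r between baseline and week-12 VISA-A, shown at 0.3, 0.5 and 0.7; and equal SDs at the two visits.

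**Step 1: the plan's own figure.** The 54 cannot be reproduced forwards because the SD is not printed. Solved backwards with the normal approximation:

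SD = 14 × √(27/2) / (1.960 + 0.842) = 18.36.

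After rounding up, any SD from 18.02 to 18.36 gives 27 per group. A t-based calculation gives 18.02, so about 18 is the implied value. The dropout step reproduces: 54 / 0.9 = 60.

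**Step 2: variance factors at week 12**, each multiplying SD² × 2/n:

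- raw difference: 1
- change from baseline: 2(1-r)
- baseline-adjusted: 1-r²

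The adjusted factor is below 1 for any r above 0. Its ratio to the change factor is (1-r²) / [2(1-r)] = (1+r)/2, which is below 1 for any r below 1. The direction therefore needs no outside figure.

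**Step 3: power and precision.** With SD 18.36 and n = 27, the raw standard error is 18.36 × √(2/27) = 5.00. Power is Φ(14/SE - 1.96), with SE = 5.00 × √factor. Each cell gives power, the 95% CI half-width in points, and the n per group needed for 80% power.

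| r | Raw week 12 | Change from baseline | Baseline-adjusted |
|---|---|---|---|
| 0.3 | 80.0%, 9.8, 27 | 65.8%, 11.6, 38 | 83.6%, 9.3, 25 |
| 0.5 | 80.0%, 9.8, 27 | 80.0%, 9.8, 27 | 89.9%, 8.5, 21 |
| 0.7 | 80.0%, 9.8, 27 | 95.1%, 7.6, 17 | 97.5%, 7.0, 14 |

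Against the better of the two planned contrasts, the gain in power is 3.6, 9.9 and 2.4 percentage points.

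**Step 4: does the GEE working correlation already recover this?** In 500 simulated trials (27 per group, complete data, r = 0.5, exchangeable structure), the GEE week-12 group difference equalled the raw difference in means to rounding error. Modelling the post-baseline visits with baseline as a covariate cut the variance to 0.72 of the raw comparison, against 0.75 in theory.

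**Step 5: chance imbalance.** With a baseline SD of 18 and 30 per group, the SE of the baseline difference is 18 × √(2/30) = 4.6 points. An imbalance of that size has these expected effects:

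- raw week-12 difference: shifted by r × 4.6 = 1.4, 2.3 and 3.2 points at r = 0.3, 0.5 and 0.7;
- change contrast: shifted the other way by (1-r) × 4.6 = 3.2, 2.3 and 1.4 points.

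The two contrasts thus differ by the full 4.6 points at any r, about a third of the 14-point target (4.6/14 = 0.33).

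**The case against.** The strongest reply is that the sentence lists effects to be tested, not a closed list of model terms. For VISA-A, with three follow-up visits, a baseline covariate would be compatible with it. Covariates are often left to a fuller document; the ethics-approved project file and any separate analysis plan are not at hand. This stands as a caution: baseline as a time level is an inference. It does not remove the point. The model is stated, it covers outcomes with a single follow-up visit, and as written it contains no adjustment.

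Second, no claim in the plan fails. The sample size was set for a between-group difference at 12 weeks, and the raw comparison delivers the planned 80% at the implied SD. That stands too.

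Three stronger readings are tempting. A reader might infer that the unadjusted analysis is biased. It is not: both contrasts are unbiased over randomization, and the shifts in step 5 are conditional on the imbalance that happens to arise. A reader might infer that baseline imbalance passes in full into the raw result; only the fraction r of it is expected to. A reader might infer that the trial is underpowered at 66%. That figure needs both r = 0.3 and the change contrast as the primary test, and the article fixes neither.

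**Conclusion.** The point holds as a nearly free improvement, not as an error that threatens validity. As written, both week-12 contrasts waste baseline information, and adjustment is more precise than either for any r strictly between 0 and 1. The size of the gain depends on an r that the article does not give. Relative to the raw comparison on which the trial was sized, variance falls by 9%, 25% or 49% at r = 0.3, 0.5 or 0.7. Relative to the change contrast it falls by 35%, 25% or 15%. Naming one adjusted contrast also removes the choice between two estimates that a chance imbalance pulls apart. The power figures rest on the back-solved SD of about 18, equal SDs at both visits and a two-sided 5% test.

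**What to change.** For VISA-A and pain, choose one of two equivalent routes and state it:

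1. Model weeks 6, 12 and 6 months with group, visit, group-by-visit, the baseline value and baseline-by-visit.
2. Keep baseline as an outcome but constrain the two group means to be equal there. In a GEE this needs a working correlation other than independence, because the baseline information enters only through it.

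In either case, report the adjusted week-12 VISA-A difference with its 95% CI as the primary contrast.

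For strength, function and SF-12, which have one follow-up visit, compare week-12 values adjusted for their own baseline. Those analyses then contain no time or group-by-time effect; use the constrained model if a time effect is still wanted. GROC has no baseline and is unaffected.

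The cost is a few sentences of specification and a revised model statement, with no extra visits, measurements or participants. Because final data collection is planned for July 2026 and the analyst is blind to allocation, the change can be documented before unblinding. If a fuller plan already contains the adjustment, the article's model statement needs only to be aligned with it.

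### The trial is sized for one week-12 VISA-A contrast at an apparently undivided 5% level, but the analysis does not name that contrast as primary and reaches it only through Bonferroni-adjusted post hoc tests

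*Protocol article*

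**What the plan says.** In the protocol article, Sample size calculation rests on "a difference between groups in the Victorian Institute of Sport Assessment-Achilles (VISA-A) at 12 weeks of 14 points", "considering a confidence level (α) of 95%, a power (β) of 80"%. On the SD it says only: "The standard deviation used in the calculations was obtained from a similar clinical trial". It reports that "calculations for linear mixed models indicated a sample size of 54 individuals (27 per group"), raised to 60 for 10% loss. It mentions no allowance for multiple comparisons, and does not say which model term or within-person correlation was used.

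Statistical analysis uses GEE "to identify main effects of group and time, and group-by-time interactions", and adds "Bonferroni-adjusted post hoc tests will be used when appropriate". It names no single contrast as primary and gives no number of comparisons. The Abstract repeats the GEE and Bonferroni plan.

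Under Outcomes, VISA-A is the main primary outcome, measured at baseline, week 6, week 12 and 6 months after the interventions end. The last paragraph of the Introduction counts the 6-week, 12-week and 6-month effects among the primary objectives.

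**The concern.** The contrast that was powered and the tests that are planned differ. The week-12 difference appears in the analysis only as a post hoc comparison, and those comparisons are to be Bonferroni-adjusted. Followed as written, the plan therefore tests the powered contrast at a stricter level than the one stated for the sample size.

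The other planned tests do not replace it. The group main effect averages over visits, including baseline, where randomisation makes the expected difference zero. The interaction asks whether the group difference changes over time, not what it is at week 12.

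At stake is a false negative. A true 14-point benefit, which is also the article's threshold for a clinically meaningful VISA-A improvement, could be missed in roughly 35–39% of trials instead of 20%, and the two loading programmes reported as not different.

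**Working it through.** **Inputs.** From the article: difference 14 points; 5% level; power 80%; 27 per group evaluable, 30 per group randomised; four VISA-A visits. Assumed: two-sided testing, consistent with the planned 95% confidence intervals; equal SD at each visit; exchangeable within-person correlation ρ from 0.3 to 0.7; baseline analysed as one of the four repeated measurements; equal weight for each visit in the group main effect.

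**Step 1: the plan's own figure.** The SD is missing, so 27 per group cannot be reproduced independently. Solving a two-sample t test for 80% power at n = 27 gives d = 0.777, so SD = 14/0.777 = 18.0 (18.4 by the normal approximation). The loss step does reproduce: 54/0.9 = 60.

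**Step 2: the week-12 contrast after Bonferroni.** Power = P(T > t₁₋α/(2k)), where T is noncentral t with 2n − 2 degrees of freedom and λ = 14/(SD·√(2/n)).

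- n = 27: standard error = 18.02 × √(2/27) = 4.904, λ = 2.855.
- n = 30: λ = 3.009.

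| Comparisons (k) | Level | Critical t (n = 27) | Power, 27 per group | Power, 30 per group |
|---|---|---|---|---|
| 1 | 0.0500 | 2.007 | 80% | 84% |
| 3 (post-baseline visits) | 0.0167 | 2.474 | 65% | 71% |
| 4 (all visits) | 0.0125 | 2.588 | 61% | 67% |

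The normal approximation gives 66% and 62% at 27 per group. Because the SD is anchored to the claimed 80%, the loss hardly depends on its value. Restoring 80% would take 37 per group (74 evaluable) for k = 3 or 39 per group (78 evaluable) for k = 4, against 54 planned.

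**Step 3: group main effect.** The effect is the mean of the four visit differences, with standard error SD·√[(1 + 3ρ)/4 · 2/n]. For differences 0/7/14/14 the mean is 35/4 = 8.75 points. At ρ = 0.5 the standard error is 4.904 × √0.625 = 3.877, the ratio is 2.26 and the power about 62%. Wald test, 27 per group:

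| True differences (baseline/week 6/week 12/6 months) | ρ = 0.3 | ρ = 0.5 | ρ = 0.7 |
|---|---|---|---|
| 0/0/14/0 | 17.9% | 14.7% | 12.8% |
| 0/7/14/7 | 54.4% | 43.9% | 36.8% |
| 0/7/14/14 | 73.5% | 61.7% | 52.7% |
| 0/14/14/14 | 87.4% | 77.3% | 68.2% |

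**Step 4: group-by-time interaction.** Three-degree-of-freedom Wald test with noncentrality Σ(δₜ − δ̄)² / [(2/n)·SD²·(1 − ρ)]. For 0/7/14/14 at ρ = 0.5 this is 134.75/12.03 = 11.2, so power is about 81%.

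| True differences | ρ = 0.3 | ρ = 0.5 | ρ = 0.7 |
|---|---|---|---|
| 0/0/14/0 | 69.7% | 84.8% | 97.7% |
| 0/7/14/7 | 50.5% | 66.3% | 88.6% |
| 0/7/14/14 | 65.4% | 81.2% | 96.5% |
| 0/14/14/14 | 69.7% | 84.8% | 97.7% |

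**The case against.** A reader might infer that none of the planned tests delivers 80% power. The calculations do not support that. The interaction reaches about 80% or more for three of the four patterns at ρ = 0.5, and for all four at ρ = 0.7. The group main effect passes 80% in one favourable case (0/14/14/14 at ρ = 0.3). A four-comparison Bonferroni contrast on change from baseline would have about 88% at ρ = 0.7, though only about 47% at ρ = 0.3.

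A reader might also infer a collapse to about 34%. That requires adjusting for all 28 pairs of the eight group-by-time cells, and the article states no such family. Nor does it show that the sizing was a plain unadjusted two-sample test: it cites a mixed-model calculation without the tested term. That no adjustment was made is an inference from the undivided 5%.

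It can fairly be said, too, that the size of the Bonferroni family and the decisive model term are often left to an analysis plan, and that adjusting across visits suits objectives that count three time points as primary. That answers any complaint about missing detail. It does not answer the mismatch: the sizing section fixes one contrast at 5%, while the analysis section sends that contrast to an adjusted post hoc step. An analysis plan could restore the stated power for the direct week-12 contrast only by exempting it from that adjustment.

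**Conclusion.** The point stands in a limited form. The stated 80% belongs to a week-12 VISA-A contrast at an apparently undivided 5% level, and the analysis as worded does not test that contrast at that level. As one of three or four adjusted between-group comparisons, its power is about 65% or 61% at 27 per group, and 71% or 67% if nobody is lost. The group main effect has about 53–74% power for 0/7/14/14 and 13–18% if the benefit appears only at week 12. Interaction power runs from about 50% to 98% with pattern and correlation, so no general shortfall can be claimed there; even a significant interaction does not say when, or in which direction, the groups differ.

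These figures rest on a back-solved SD of about 18, two-sided testing and assumed correlations. The 80% itself cannot be verified from the article.

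**What to change.** In Statistical analysis, name the week-12 between-group VISA-A difference, estimated from the GEE, as the single primary test at two-sided 5%. State that it does not depend on an omnibus test and is not Bonferroni-adjusted. Confine Bonferroni to the other contrasts (week 6, 6 months). Do not use a group main effect that includes baseline as a test of efficacy. In Sample size calculation, add the SD, the correlation and the tested term.

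This needs no extra participants, but it is more than a wording change to one section: week 6 and 6 months, now among the primary objectives, become secondary for testing, and the Introduction should be aligned.

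If the sponsor prefers to keep the Bonferroni-adjusted comparisons as decisive, state the number of comparisons and restate the power at the adjusted level: about 65% for three and 61% for four at 27 per group, on the assumptions above.
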